### Statistical Issues

#### Sample size

For the primary RCT we have estimated the sample size for the primary outcome of objective walking capacity based on an estimate of the difference in the proportion of participants who achieve a MCID in walking distance. Since the MCID for the SPWT is unknown we will estimate it to be an improvement in walking distance from baseline of 30 % or more. We estimate a total of 30 % of participants will achieve the estimated MCID in Group 2 and 60 % in Group 1. Based on an estimate of 30 % difference in proportions, a power of 0.8, an alpha of 0.05 and an estimated drop-out rate of 20 %, a minimum of 52 participants per group is estimated to be required to achieve significance using a two-tailed *t*-test for two independent proportions [60]. Our primary end point will be the 6-month follow-up.

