#### Statistical analysis

Baseline status of treatment groups will be compared using two-tailed independent samples t tests, Chi squared tests of independence, and Mann-Whitney U tests as indicated. Our analyses will be based on the “intention to treat” principle. Data will contain repeated measurements of the main response variables.

We will analyze the primary outcome (SPWT) by calculating the differences in proportions meeting the MCID using Pearson Chi Squared test with 95 % confidence intervals. To control for potential confounding (sex, education, perceived health status, dominant leg or back pain, and hospital), logistic regression models and generalized estimation equation (GEE) methods will be used [5]. These models will control for baseline differences not balanced by randomization. Dichotomous secondary outcomes will be analyzed similarly.

For continuous secondary outcomes we will first compute the group-specific mean, standard deviation and median at each follow-up interval. Second, we will build ordinary least-square (OLS) models using generalized estimating equation to account for the autocorrelation present in the outcomes [5]. Third, we will test whether the group effects are constant throughout the follow-up periods [5]. Fourth, we will test whether imbalances in the distribution of the baseline covariates confound the group effects. Covariates added to the crude linear model that change any of group regression coefficients by 10 % percent or more will be retained as confounders in the adjusted models [61]. The group effects will be reported as the mean differences and 95 % for each follow-up interval.

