We have included a 1-month booster session following the 6-week training program. This emulates our current practice protocol at our Spinal Stenosis Clinic at Mount Sinai Hospital. The rationale being that LSS is a chronic condition and patients may benefit from periodic monitoring of their self-management skills and abilities. Periodic reassurance and positive reinforcement may also be of benefit especially among patients with underlying psychosocial barriers such as poor coping skills that accentuate functional limitations. Periodic monitoring and coaching may help to improve longer-term outcomes.

A leading cause of failure of RCTs is the lack of enrollment of sufficient number of participants into the study. We have enlisted a large referral source for potential participants. LSS is a very common condition seen by neurosurgeons and orthopedic spine surgeons, rheumatologists, physiatrists, family physicians and chiropractors. If our enrollment is deemed slow, we will expand our referral source to the University of Toronto vascular surgeons who also see a large number of patients with neurogenic claudication caused by LSS. We will also advertise in local newspapers and seniors publications. In addition, we will distribute pamphlets to be placed in-patient waiting areas at participating hospital clinics and in community clinics. Compliance to follow-ups may be problematic and we plan to provide incentives in the form of covering transportation costs up to $25 per day.

We anticipate that assessor blinding (to assigned intervention) during follow-up assessments will be challenging. We will implement strict rules preventing the communication, regarding participant allocation among participants, the research coordinator and blinded assessors.

Study design limitations include the lack of blinding of both practitioners and patients and this can introduce bias. The multi-modal and pragmatic nature of the design prohibits the determination of the component(s) of the intervention that may be responsible for potential improvements. There is potential for participants to receive other interventions during the intervention and between follow-up periods, which may impact the results. We will compare co-interventions receive between group and comment on the potential impact they may have on the results.

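### Least-squares GEE for the continuous secondary outcomes, read literally, relies on dropout unrelated to earlier scores; a mixed model that includes baseline would relax this at little cost

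*Protocol article*

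**What the plan says.** Under Statistical analysis, the step for continuous secondary outcomes reads "we will build ordinary least-square (OLS) models using generalized estimating equation to account for the autocorrelation present in the outcomes". The same paragraph then tests whether group effects are constant over follow-up. It retains baseline covariates that change a group coefficient by 10 % or more, and reports mean differences for each follow-up. It names no working correlation, weighting, imputation or assumption about missing data. It does not say that the baseline value of the outcome is always in the model.

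On loss to follow-up, Sample size allows for "an estimated drop-out rate of 20" %, in a calculation for the walking test. The Discussion says "Compliance to follow-ups may be problematic" and, in the same sentence, offers to cover transport costs. It also warns that the burden of the walking test may raise dropout. Data collection and follow-up provides for all self-report measures to be taken by telephone when a participant cannot attend.

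**The concern.** Least squares combined with GEE is, on its face, the independence working model. With group, visit and group-by-visit terms, the crude estimate at a visit is the difference in observed means among those still in the study. GEE then corrects only the standard error. The earlier scores of people who later leave do not inform the later point estimates.

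That is harmless if leaving is unrelated to earlier scores, given the covariates. If people who are doing poorly leave, and more selectively in one arm, the later comparisons are between selected groups. Patients are not blinded, and the arms differ in contact (twelve sessions and a booster against one session), so such dropout is plausible, though not established. The outcomes concerned are the ZCQ scales, ODI, pain scores, SF-36, CES-D, SPPB and FES. The Discussion relies on the ZCQ function scale in particular to offset missed walking tests.

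**Working it through.** **1. The plan's own figure.** Inputs from Sample size: 30 % and 60 % responders, "a power of 0.8, an alpha of 0.05", two-tailed, 20 % dropout.

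- Pooled-variance formula: n = [1.960·√(2·0.45·0.55) + 0.842·√(0.6·0.4 + 0.3·0.7)]² / 0.30² = [1.379 + 0.565]² / 0.09 ≈ 42 per group.
- Dropout: 42 / 0.80 = 52.5, so 53. Using 42 × 1.2 instead gives 51.

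The stated 52 is reproduced to within one participant. Nothing below changes it.

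**2. Assumptions for the size of the bias.** None of these comes from the document: four follow-ups, SD 1, higher score better, correlation 0.7 between visits, true difference 0.40 SD at every visit, no loss before the first follow-up. Dropout is monotone. In the one-arm case the Group 2 chance of leaving follows logit(p) = −2.35 − 1.0 × previous score and is constant in Group 1. About 22 % and 19 % are then missing at the third follow-up (6 months).

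**3. Results for a true 0.40 SD at 6 months** (simulation, mostly with very large arms to isolate bias):

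| Dropout mechanism | OLS / independence GEE | Likelihood model |
|---|---|---|
| Random | agrees with truth | agrees with truth |
| Rates differ by arm only (13 % v 28 %) | 0.40 | – |
| Depends on score, same slope in both arms, about 20 % lost | 0.35 to 0.38 | 0.40 |
| Same slope, about 10 % lost | 0.39 | – |
| Depends on score in Group 2 only, about 20 % lost | 0.25 to 0.27 | 0.39 to 0.41 |
| Group 2 only, about 10 % lost | 0.33 | – |

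The bias at about 20 % loss is therefore 0.40 − 0.38 = 0.02 to 0.40 − 0.35 = 0.05 SD with equal slopes, and up to 0.40 − 0.25 = 0.15 SD with one-arm dependence. In the one-arm case the independence estimate at 12 months is about 0.20. With no true effect it is −0.13 to −0.15 at 6 months, against about 0.00 from the likelihood model.

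**4. Working correlation.** In the one-arm case an exchangeable working correlation gave about 0.39. A second set of simulations used a true 0.50 SD, exchangeable or AR(1) data, correlation 0.5 or 0.7, and 20 % lost by the last visit. Over all its dropout mechanisms, exchangeable GEE gave 0.48 to 0.54 at the last visit and the mixed model about 0.50 to 0.51. Independence GEE gave 0.45 to 0.48 with equal slopes, 0.34 to 0.43 with dependence in one arm, and 0.15 to 0.36 with opposite slopes.

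**5. Baseline score.** If the baseline score enters the least-squares model, the one-arm estimate rises from 0.25 to 0.35. A mixed model does not remove the need for it. When loss before the first follow-up also depends on baseline in one arm, a mixed model of follow-up visits alone gives 0.33 for a true 0.40, and adding baseline restores 0.40.

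**The case against.** The strongest reply is that the text does not settle on the independence form. It says GEE is there to handle autocorrelation. *OLS* may be loose wording for a linear model, as against the logistic models of the preceding paragraph. The working correlation, weighting and imputation may also sit in an analysis plan that is not shown. This stands in part: with an exchangeable structure most of the bias goes. But the sentence names least squares and no other structure, so the literal reading is the exposed one, and one edit settles it.

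Three stronger readings are tempting, and the document supports none of them:

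- *A fifth of these outcomes will be lost.* The 20 % is an allowance for the walking test. Of the outcomes listed, all but the SPPB can be taken by telephone. Telephone contact does not help with participants who withdraw or cannot be reached.
- *The unequal number of visits biases the comparison by itself.* Dropout rates that differ only by arm leave the estimate at 0.40. The bias needs dropout that depends on earlier scores.
- *About a third of the effect will disappear.* That follows only from strong score-dependence in one arm and none in the other. With equal slopes the loss is 0.02 to 0.05 SD.

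It is also fair to say that GEE is a standard method and that only secondary outcomes are involved.

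**Conclusion.** The point holds as a cheap improvement to the secondary analyses, not as an error that threatens the trial. Read literally, the named model needs dropout to be unrelated to earlier scores given its covariates. A correctly specified likelihood model needs only that dropout be explained by observed data. The bias could be anywhere from nil to about 0.15 SD at 6 months for a true 0.40 SD, depending on the assumed dropout mechanism, the correlation of 0.7 and roughly 20 % loss. It could be larger if the two arms select in opposite directions. It is small if a non-independence working correlation is what was meant. The SPPB is the most exposed outcome because it has to be done in person. The primary responder analysis and the sample size are untouched.

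**What to change.** Replace the OLS/GEE sentence with wording such as: *Continuous secondary outcomes will be analysed with a linear mixed model for repeated measures, with group, visit, group-by-visit, and the baseline value of the outcome with its interaction with visit. Within-person covariance will be unstructured, with a pre-stated simpler structure if the model does not converge. Estimation will be by REML with Kenward-Roger degrees of freedom. The group difference and 95 % CI will be reported at each visit.*

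Alternatively, enter baseline as an additional outcome with a common mean in both arms, so that participants with no follow-up also contribute. Keep GEE as a sensitivity analysis and state its working correlation.

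The cost is analysis wording only: same data, same per-visit differences, same sample size, standard software. The downside is that a covariance model must be specified and fitted, and dropout that depends on unobserved scores is still not covered.

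### For the continuous secondary outcomes, adjustment covariates are chosen by observed imbalance and a 10 % change in the group coefficient, and the baseline value of the outcome is not fixed in the model

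*Protocol article*

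**What the plan says.** All of this is in the Statistical analysis section of the protocol article.

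- **Baseline comparison:** "Baseline status of treatment groups will be compared using two-tailed independent samples t tests, Chi squared tests of independence, and Mann-Whitney U tests" are planned between the randomized groups.
- **Primary outcome** (response on the self-paced walking test, SPWT): the first analysis is unadjusted, "calculating the differences in proportions meeting the MCID using Pearson Chi Squared test with 95 % confidence intervals". Logistic and GEE models follow for named potential confounders ("sex, education, perceived health status, dominant leg or back pain, and hospital"). The article adds: "These models will control for baseline differences not balanced by randomization".
- **Continuous secondary outcomes:** "we will build ordinary least-square (OLS) models using generalized estimating equation to account for the autocorrelation present in the outcomes". Then "we will test whether imbalances in the distribution of the baseline covariates confound the group effects", and covariates "that change any of group regression coefficients by 10 % percent or more will be retained as confounders in the adjusted models".

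The baseline value of the outcome is neither in the named list nor stated as a term in the continuous-outcome models. The section on randomization and Table 2 show that the SPWT, the questionnaires and the physical performance battery are all completed before allocation, so these values are available for every participant.

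**The concern.** Allocation is random and follows all baseline measurement, so any baseline difference between the groups is chance. Testing for it, or screening covariates for confounding, answers a question that belongs to observational data. What matters in a trial is how strongly a covariate predicts the outcome, and that can be decided in advance.

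The 10 % threshold is also relative to the estimated group effect. When the effect looks small, the bar is low and more covariates enter. When it looks large, the bar is high, and a strongly predictive covariate that happens to be balanced is removed. The model that yields the adjusted effect therefore depends on the effect itself, and precision already paid for at baseline can be lost.

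The procedure produces a crude and an adjusted result for each outcome, and the article does not say which is the main one. At stake are the precision and the pre-specification of the secondary outcomes, which carry the functional part of the hypothesis.

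**Working it through.** **Inputs from the article (Sample size).** Response 60 % v 30 %, two-sided alpha 0.05, power 0.80, dropout 20 %, 52 per group.

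**Assumed, because the article gives no figure.** Baseline-to-follow-up correlation r = 0.5, 0.6 or 0.7; group difference 0.5 SD; six further covariates unrelated to outcome; one follow-up time.

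**1. The plan's own figure.** With pooled variance and mean proportion 0.45:

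n = [1.96 × √(2 × 0.45 × 0.55) + 0.8416 × √(0.60 × 0.40 + 0.30 × 0.70)]² / 0.30² = 41.97, so 42 per arm.

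With dropout, 41.97 / 0.8 = 52.46, which agrees with 52. The working number is therefore 42 evaluable per arm.

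**2. Power with and without baseline.** Approximate power is Φ(0.5 / [√(2/42) × √(1 − r²)] − 1.96), with √(2/42) = 0.218. Without baseline, r is set to 0.

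- No baseline: 63 %
- Baseline fixed: 75 % (r = 0.5), 82 % (r = 0.6), 89 % (r = 0.7)

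**3. How often the screen drops baseline.** Adding one covariate moves the group coefficient by its slope times the between-group difference D in that covariate. In SD units, baseline is dropped when r × |D| < 0.1 × |effect|. Taking the estimated effect as 0.5, this is |D| < 0.05 / r. D has SD 0.218, so the chance of dropping baseline is P(|Z| < 0.05 / (0.218 × r)): 35 %, 30 % and 26 % for r = 0.5, 0.6 and 0.7.

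**4. Simulation of the whole rule** (42 per arm, 0.5 SD, baseline plus six irrelevant covariates):

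| r | Crude power | 10 % rule | Baseline always fixed | Baseline dropped |
|---|---|---|---|---|
| 0.5 | 62 % | 69 % | 73 % | 38 % |
| 0.6 | 61 % | 75 % | 80 % | 29 % |
| 0.7 | 63 % | 83 % | 88 % | 26 % |

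The rule loses 73 − 69 = 4, 80 − 75 = 5 and 88 − 83 = 5 points against fixed adjustment. Other runs of the same design gave 3 to 6. If baseline never enters, the loss is 73 − 62 = 11, 80 − 61 = 19 and 88 − 63 = 25 points.

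**5. Dependence on the result.** The rule keeps about 3.3 of 7 candidates on average with no effect and about 1.3 of 7 at 0.5 SD.

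**6. Several follow-ups.** The rule is met if any one group coefficient moves. With four visits (inter-visit correlation 0.7 assumed), about 5 of 7 are kept under the null and about 2 of 7 at 0.5 SD. Baseline is dropped in about 19 to 29 % of trials, and the loss remains about 3 to 5 points.

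**7. Type I error.** The crude, screened and fixed analyses each stay near 5 %. Taking the smaller of the crude and screened p-values gives about 7 to 8 % (0.070, 0.081 and 0.073 in three settings with baseline and five weakly predictive covariates).

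**The case against.** **The primary result is not chosen by the data.** A reader might infer that the 10 % rule governs the reported primary effect. It does not. The rule stands in the paragraph on continuous secondary outcomes. The primary analysis starts with a fixed unadjusted chi-squared test, on which the sample size rests, and its adjusted models have covariates named in advance. The sentence on baseline differences can be read as the purpose of that list, and nothing says that the baseline tests select covariates for it. This stands; only a loose tie to observed imbalance remains in the supporting adjusted model.

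**The absence of baseline SPWT from the primary model is not a defect of the same weight.** Response is an improvement of at least 30 % from baseline, so baseline already enters the endpoint. The power figures above are for continuous outcomes and do not carry over. This stands.

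**Dropping baseline does not leave a large bias.** One might infer that serious chance imbalance stays in the estimate. In a one-at-a-time screen, a dropped covariate would have moved each group coefficient by less than 10 %, so what remains is small by construction. The cost is precision. Nor does almost every covariate pass near the null: it is about 3 of 7, or about 5 of 7 with four visits.

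**A condensed article may leave baseline handling to the analysis plan.** It does not say whether the response is a change or a raw score, whether baseline is one of the repeated measurements, or whether it is a candidate for the screen. This stands in part: silence alone would be no finding. The selection rule, however, is explicit, and an analysis plan that followed it would inherit the problem.

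**Conclusion.** The point holds for the adjusted models of the continuous secondary outcomes. The article states a selection rule driven by observed imbalance and by the estimated effect, and it does not secure the baseline value of the outcome as a model term.

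The loss is modest if baseline is screened and substantial at the higher correlations if baseline is left out altogether. These sizes rest on the assumed correlations, effect and covariates; the direction does not. The rule by itself does not inflate type I error. The inflation arises only if the choice between crude and adjusted results stays open, which the article allows by not naming a main estimate.

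The primary chi-squared test and the planned 52 per group are untouched. This is a change that should be made, not a flaw that invalidates the trial.

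**What to change.** - Delete the 10 % rule, and do not use tests of baseline imbalance to choose covariates. A descriptive baseline table is enough.
- State in advance that every continuous-outcome model contains the baseline value of that outcome, group, time and group-by-time, plus a short named covariate list that is kept whatever the observed balance. Part of this is already implied, since the article plans to test whether group effects are constant over follow-up and to report a difference for each interval.
- Name this model as the main estimate for each outcome and report the unadjusted result alongside.
- For the adjusted primary model, keep the named list regardless of observed balance and reword the sentence on baseline differences to match. Adding baseline SPWT distance is optional.

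The cost is wording only: the baseline values are already collected, and the sample size does not change.

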### Protection of human subjects and assessment of safety

#### Protection of human subjects

The Mount Sinai Hospital (MSH) Research Ethics Board has approved the study protocol (certificate number 14-0020).

#### Adverse events

We will measure the presence of adverse events that may be associated with each of the interventions. This will take place following each visit for participants enrolled in Group 1. For participants enrolled in Group 1 and 2, adverse events will be assessed at each follow-up visit. We will define adverse events as an unintended sign or symptom of the intervention. These include: significant increase in back and/or lower extremity pain, numbness, tingling, tiredness or claudication and cauda equine syndrome. We will compute the incidence (95 % CI) of each adverse event listed above. The cumulative number of visits will be used as the denominator. Any adverse event that is life threatening or associated with significant disability will be reported to the Mount Sinai Hospital Ethics Review Board.

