We have designed and implemented a training program for LSS known as the Boot Camp Program for LSS [24]. This program aims to address the multi-faceted aspects of LSS using a multi-modal non-surgical approach with a focus on self-management and the goals of improved walking ability, overall functional status and quality of life. The program considers the dynamic nature of LSS where symptoms change relative to posture. Reduction of the lumbar lordosis while standing, walking and sitting reduces epidural pressure and improves blood flows to spinal nerves [3, 11]. Enabling patients to introduce inter-segmental lumbar spine flexion (reducing the lumbar lordosis) using anterior pelvic tilt may reduce symptoms and improve walking ability [25–27]. Individuals with LSS tend to be deconditioned due to inability to walk and consequential sedentary lifestyle and may not have the necessary core strength and lumbar flexibility to accomplish this body realignment. They can also have reduced lower extremity strength due to combined nerve root compression and disuse. Specific flexibility, aerobic and core and lower extremity strengthening exercises, manual therapy and postural instruction may overcome these deficiencies.

The program also considers potential psychosocial consequences of LSS and incorporates a cognitive behavioral approach [28, 29]. This approach aims to improve coping and problem solving, build self-efficacy, provide feedback and develop realistic treatment and functional goals. Since LSS is a chronic and often-progressive condition [30] the program emphasizes incorporating learned physical and psychosocial self-management strategies for life. Patients receive an instructional workbook and video as part of the training program. The workbook and video provide education on self-management strategies and instruction on how to perform all the specific exercises and body realignment techniques. The workbook incorporates a schedule outlining the intensity and frequency of each exercise with goals tailored to each patient. The training program also includes a pedometer that provides weekly feedback for both patients and practitioners on walking ability.

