### Data collection and follow-up

Table 2 summarizes the data to be collected during the trial. We will follow-up with participants at 6 weeks, and 3, 6 and 12 months following randomization. A trained blinded assessor will conduct all follow-up assessments at the study site. Should patients be unable to attend a follow-up in person, all self-report measures will be administered via telephone. All assessors will receive training in order to standardize assessments and minimize inter- and intra-assessor variability. The assessors will be blinded to the treatment allocation and will be responsible for all follow-up assessment per assigned participant. The following outcomes will be measured at each follow-up.

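### The adverse event definition requires a causal link to treatment but names no judge of it, and only Group 1 is also asked at unblinded treatment visits, so attribution may differ between arms

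*Protocol article*

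**What the plan says.** All of the following is in the protocol article.

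- **Scope and definition (Adverse events).** The section opens: "We will measure the presence of adverse events that may be associated with each of the interventions". It then defines the term: "We will define adverse events as an unintended sign or symptom of the intervention". The examples are a significant increase in back or leg pain, numbness, tingling, tiredness or claudication, and cauda equina syndrome.
- **Collection (Adverse events).** "This will take place following each visit for participants enrolled in Group 1". And: "For participants enrolled in Group 1 and 2, adverse events will be assessed at each follow-up visit".
- **Analysis and reporting (Adverse events).** The incidence of each listed event is to be given with a 95 % confidence interval, with cumulative visits as denominator. Life-threatening or significantly disabling adverse events go to the ethics board. No between-arm test of harms is stated.
- **Follow-up (Data collection and follow-up).** "A trained blinded assessor will conduct all follow-up assessments at the study site". "The assessors will be blinded to the treatment allocation and will be responsible for all follow-up assessment per assigned participant".
- **Blinding (Discussion).** "Study design limitations include the lack of blinding of both practitioners and patients and this can introduce bias". The Discussion also promises strict rules against communicating allocation to the assessors.
- **Disease course (Background).** "Since LSS is a chronic and often-progressive condition".
- **Group 2 safeguard (Discussion).** The plan anticipates that single-session participants may do the exercises wrongly and be injured. It offers them a safety monitoring protocol and a way to contact the team.

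**The concern.** Under the definition as written, a worsening that nobody blames on treatment is not an adverse event. That makes attribution a filter on the count. The filter is hard to apply here, because more leg pain, numbness or claudication may be a reaction to treatment or the natural course of the condition, and the two look alike.

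The setting of that judgement differs by arm. In Group 1 many of the questions come straight after a session that included manual therapy, from people who know what was given. In Group 2 the scheduled questions come weeks to months after one session without manual therapy, at a visit run by someone who must not know the arm. A person who does not know which intervention was given is poorly placed to say whether a symptom arose from it.

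Three things are at stake:

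1. The incidences printed side by side may reflect how readily symptoms are blamed on treatment as well as how often they occur.
2. If the assessor is drawn into the causal question, assessor blinding comes under pressure, and the same follow-ups carry the primary walking test.
3. The ethics-board rule is written in terms of adverse events, so it inherits the causal condition.

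**Working it through.** The plan gives no adverse event rate and no precision target for harms, so there is no planned figure to reproduce. The check has three parts.

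**1. The two thresholds side by side.** The opening sentence of Adverse events covers events that could be linked to an intervention. The definition covers only those that are signs or symptoms of it. The second is narrower, and the section does not say which governs the count.

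**2. Scheduled collection points per participant.** Inputs: 12 sessions and 1 booster (Group 1 section), 1 session (Group 2 section), 4 follow-ups (Data collection and follow-up).

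- Group 1: 12 + 1 + 4 = 17, of which 12 + 1 = 13 are treatment visits with allocation known; 13/17 = 76 %.
- Group 2: 4, all follow-ups. No collection is scheduled after the single session.

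The 13 treatment visits fall within about 6 + 4 = 10 weeks of a 12-month trial. After that, scheduled collection is the same in both arms.

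**3. What differential attribution could do (all rates assumed).** Let both arms have the same true number of worsenings. Let a share *s* of Group 1's be met first at treatment visits. Let *a_u* be the probability of attribution at an unblinded treatment visit and *a_b* the probability at a blinded follow-up. Then

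Group 1 / Group 2 count ratio = [*s*·*a_u* + (1 − *s*)·*a_b*] / *a_b*.

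| *a_u* | *a_b* | *s* = 0.3 | *s* = 0.5 | *s* = 0.7 |
|---|---|---|---|---|
| 0.8 | 0.8 | 1.00 | 1.00 | 1.00 |
| 0.8 | 0.5 | 1.18 | 1.30 | 1.42 |
| 0.8 | 0.2 | 1.90 | 2.50 | 3.10 |
| 0.5 | 0.8 | 0.89 | 0.81 | 0.74 |

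Example from the third row: (0.5 × 0.8 + 0.5 × 0.2)/0.2 = 0.50/0.20 = 2.50.

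A cruder illustration applies one attribution rate to a whole arm. Take 52 per arm (the planned size), 30 % truly worsening in each, and 60 % of worsenings attributed in Group 1. Counted rate = true rate × attribution rate, so Group 1 is 0.30 × 0.60 = 18 %.

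| Group 2 attribution | Group 2 counted rate | Spurious risk ratio | Rejection, two-sided 5 % Pearson chi-squared (exact) |
|---|---|---|---|
| 60 % | 18 % | 1.0 | 0.049 |
| 40 % | 12 % | 1.5 | 0.132 |
| 30 % | 9 % | 2.0 | 0.263 |
| 20 % | 6 % | 3.0 | 0.478 |

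The plan states no such test, and a single rate for all Group 1 events ignores the 10-week limit in part 2. These figures show only that moderate differences in attribution could matter. They do not estimate what will happen in this trial.

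**The case against.** The strongest reply is that no attribution step is actually described. The section opens with events that could be associated with treatment, names concrete symptoms and counts each of them. Staff might simply record a listed symptom when it is present. That reading is possible, but the defining sentence says otherwise, so the text still needs to be settled.

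Four stronger readings are tempting, and the documents do not support them.

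- *The blinded assessor must judge cause.* A reader might infer this from the follow-up and adverse event sections taken together. No section says who decides. It could be the coordinator, who holds the allocation envelopes, and an article may leave such detail to a fuller protocol.
- *Every Group 2 event passes through that assessor.* The Discussion gives Group 2 a contact route and safety monitoring. Group 1 events reported at follow-up also arise in the same blinded visits.
- *The harm comparison is biased.* The bias is a risk. It vanishes if attribution is equal and reverses if attribution is stricter in Group 1. No formal between-arm harm test is planned.
- *Worsening in Group 2 would go unrecorded.* Pain while walking, Zurich Claudication Questionnaire symptoms (including numbness and weakness), disability and walking distance are measured in both arms at the same follow-ups whatever the cause. Tiredness as a listed event and cauda equina syndrome are not obviously covered in this way.

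The unequal number of collection points and the visit denominator are separate matters, documented more directly. Correcting them would leave the causal condition in place.

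**Conclusion.** The point holds as a risk built into the wording. The definition is causal, most of the listed events mimic the disease, unblinded collection occurs in one arm only (13 of 17 scheduled points, against none of 4), and no judge of causation is named. Applying the stated rule could make the counts depend on the arm, may put pressure on assessor blinding, and carries the causal condition into ethics-board reporting. Incidences with confidence intervals in a two-arm trial will be read comparatively even without a test.

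The direction and size are unknown. The count ratios of 0.74 to 3.10 and the rejection rates of 13 % to 48 % rest wholly on assumed attribution rates, and the latter also on a test that the plan does not contain. The planned sample size is unaffected. The change is worth making because it is cheap and removes the dependence on attribution. The documents do not show that a bias will occur.

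**What to change.** In the Adverse events section:

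1. Define an adverse event as any new or worsened sign or symptom since baseline, regardless of presumed cause, and bring the opening sentence into line with this.
2. Compare the arms on these all-cause events, asked with the same questions at the four follow-ups common to both.
3. Report events elicited at Group 1 treatment sessions separately, as a description of that arm only.
4. Record relatedness as a separate descriptive item, completed by existing staff other than the blinded assessor.
5. Reconcile the ethics-board reporting sentence with the revised definition.

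The cost is one changed definition and a small edit to the adverse event form, with no extra visits, staff or participants. The downside is that both arms will show higher counts that include background worsening of the disease, and somewhat more events may reach the ethics board. Because the disease course is common to both arms under randomization, the all-cause counts still support a fair comparison between them.
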